### 2.2.5.1. Theoretical basis

The intervention is based on Social Cognitive Theory, which emphasizes a triadic, reciprocally deterministic relationship between the individual, environment, and behavior. It recognizes that behavior change is a dynamic process that moves at variable speed through stages of readiness to change. Positive outcome expectancies through realistic goal setting and guided action planning are associated with initiation of behavior change. Self-efficacy developed for specific behaviors (e.g., physical activity) predict establishment and maintenance of behavior change. Social Cognitive Theory suggests that self-efficacy is enhanced through social support and gradual mastery of self-regulation skills (e.g., goal setting, self-monitoring).

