### 2.2.8.2. Potential effect modifiers and mediators (Aim 2)

To complement the primary and secondary outcomes, we will explore for whom and under what condition (effect modifiers) and how (effect mediators) treatment effects occur. Potential modifiers include sociodemographics (e.g., age, sex, education, employment, occupation, marital status, household size, income, country of origin), food insecurity, acculturation, and health literacy. Potential mediators include self-efficacy, social support, and intervention adherence. Intervention adherence will be tracked using session attendance, self-monitoring data, and communication between the participant and coach.

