Subgroup analyses of pre-specified potential modifiers (**Table 2**) of the intervention effect on weight change will be performed by expanding equation 1 to include the appropriate modifier-by-study-arm interactions. Testing whether the  $\beta$  coefficients of the interaction terms are equal to zero is equivalent to testing the null hypothesis that the subgroup of interest does not independently modify the intervention effect.

Longitudinal (e.g., change in mediator from baseline to 12 months and change in primary outcome from 12 to 24 months) and contemporaneous (e.g., changes in mediator and outcome from baseline to 24 months) mediation will be examined separately by MacKinnon's product of coefficients test ( $\alpha\beta$ ). Asymmetric confidence limits will be constructed based on the distribution of the product with the PRODCLIN program. Because multi-collinearity may be present in multiple mediator models, we first will test each mediator in single-mediator models. Multiple-mediator models including all variables that are at least marginally significant in the single-mediator models will test for independent and suppression effects. To determine the extent of mediated effect, the percentage of total effect mediated will be calculated for each significant mediator as  $\alpha\beta/(\alpha\beta + \gamma)$ , where  $\gamma$  is the direct intervention effect on outcome. The effect modification-mediation analyses are hypothesis generating only, but we pre-specify the variables to ensure a focus.

We will analyze the quantitative process data using standard tests (e.g., Student's  $t$ -tests for continuous variables and  $\chi^2$  tests for categorical variables). These analyses will be descriptive and not inferential. We will transcribe, code, and analyze qualitative data using Atlas.ti. We will develop a codebook of codes and definitions based on the RE-AIM domains assessed, and use it to train coders and guide data coding. To identify themes we will use content analysis methods. We will triangulate data from different sources to increase the validity of the qualitative data and to draw conclusions about reach, adoption, implementation, and maintenance of the intervention that would guide future implementations.

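### Screening mediators on single-mediator significance works against the stated aim of testing suppression, and can bias the retained mediated effect

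*Protocol*

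**What the plan says.** Section 2.2.9.1 of the protocol tests mediation by the product of coefficients, in two stages. The reason given for the first stage is collinearity: "Because multi-collinearity may be present in multiple mediator models, we first will test each mediator in single-mediator models". The second stage is limited by the results of the first: "Multiple-mediator models including all variables that are at least marginally significant in the single-mediator models will test for independent and suppression effects". The significance level for entry is not given, and no joint model without the screen is described. Reporting also depends on significance: "the percentage of total effect mediated will be calculated for each significant mediator". The whole exercise is labelled exploratory: "The effect modification-mediation analyses are hypothesis generating only, but we pre-specify the variables to ensure a focus".

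Section 2.2.8.2 names self-efficacy, social support and intervention adherence as the candidate mediators. Table 2 lists two self-efficacy instruments, one social-support instrument, and three adherence counts classed as intervention process measures. Section 2.2.5.1 gives a reason to expect correlation between the first two constructs: "Social Cognitive Theory suggests that self-efficacy is enhanced through social support and gradual mastery of self-regulation skills".

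**The concern.** In its classic form, suppression means that a variable's effect is hidden when it is examined alone and emerges only with a correlated variable in the model. A rule that admits variables on their stand-alone result tends to remove those very variables. If only one mediator passes, no multiple-mediator model is left to fit.

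There is a second consequence. When the dropped mediator is correlated with a retained one and itself affects weight, the retained coefficient absorbs part of the missing path. Its indirect effect and percentage mediated are then wrong.

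Aim 2 asks how the intervention works. A real opposing pathway could be reported as absent, and the size of the pathway that remains could be misstated.

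**Working it through.** **The protocol's own figure.** There is none for mediation. The sample-size statement in section 2.2.9.2 serves only to set the number analysed. For 2.1 kg, SD 4.6 kg, two-sided 5% and 80% power, n = 2(1.960 + 0.842)² × 4.6²/2.1² = 75.3, so 76 evaluable per arm, and 76/0.8 = 95 against the stated 93. That is close enough and is not at issue. With 20% loss, 0.8 × 186 = 148.8, so 148 participants (74 per arm) are used below.

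**Algebra.** Let mediators M1 and M2 have unit residual variance and residual correlation ρ given arm, with joint-model paths b1 and b2 to weight.
- M2 tested alone has coefficient b2 + ρ·b1. This is zero when b2 = -ρ·b1, although b2 is not zero.
- If M2 is dropped, M1 has coefficient b1 + ρ·b2 instead of b1.

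Take b1 = -0.5, b2 = +0.3, ρ = 0.6. M2 alone: 0.3 + 0.6 × (-0.5) = 0.00, the exact cancellation point. M1 alone: -0.5 + 0.6 × 0.3 = -0.32. With an arm effect of 0.5 SD on each mediator, the indirect effect through M1 is 0.5 × (-0.32) = -0.16 instead of 0.5 × (-0.5) = -0.25, which is 36% too small.

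**Percentage mediated in that setting.** Assume a direct effect of -0.2. The total is -0.2 - 0.25 + 0.15 = -0.30. M1 alone gives 0.16/0.30 = 53%. In the joint model M1 carries 0.25/0.30 = 83% of the total and M2 carries -50%, so percentages are hard to read when signs oppose.

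**Simulation.** Assumptions: 148 participants; entry if both paths have p < 0.10 alone; M2 counted as detected if both of its paths have p < 0.05 in the joint model; arm effect on each mediator 0.5 or 0.6 SD. The 0.6 SD runs used mirrored signs (4,000 trials per setting, simulation error below one percentage point), which does not affect detection. Entries are the percentage of trials detecting M2, without screen → with screen.

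| Paths M1 / M2 | ρ | M2 alone | Arm effect 0.5 SD | Arm effect 0.6 SD |
|---|---|---|---|---|
| -0.5 / +0.3 | 0.6 | 0.00 | 69 → 3 | 77 → 5 |
| -0.5 / +0.25 | 0.5 | 0.00 | not run | 70 → 5 |
| -0.4 / +0.12 | 0.3 | 0.00 | not run | 26 → 5 |
| -0.5 / +0.4 | 0.5 | +0.15 | 83 → 37 | 94 → 45 |
| -0.5 / +0.5 | 0.6 | +0.20 | not run | 95 → 44 |
| -0.4 / +0.4 | 0.3 | +0.28 | not run | 95 → 80 |
| -0.5 / +0.5 | 0.3 | +0.35 | 85 → 76 | 95 → 90 |
| -0.3 / -0.3 | 0.6 | -0.48 | 70 → 66 | not run |

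**Retained effect (0.6 SD runs, absolute values).** In the three cancellation settings, the mean M1 indirect effect after the screen is 0.209 (true 0.300), 0.236 (true 0.300) and 0.223 (true 0.240), that is 30%, 21% and 7% too small. A strong mediator with no relevant omitted partner is hardly changed (0.303, true 0.300). A weak one kept because it was significant is inflated (0.096-0.097, true 0.060).

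**Collinearity.** Two mediators correlated at 0.6 have a variance inflation factor of 1/(1 - 0.36) = 1.6, so standard errors grow by √1.6, about 1.25 times. Significance in a single-mediator model does not measure collinearity: two strongly correlated mediators can both pass.

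**The case against.** A reader might infer that the plan cannot detect suppression at all. It can: where opposing mediators each show an effect alone, 76-90% detection remains with the screen in the settings run. The protocol does not define suppression narrowly, and that form stays testable. A reader might also infer that every retained effect is distorted. That holds only when a dropped mediator is correlated with a retained one and affects weight, or when a weak effect is kept because it reached significance.

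The sharpest figures come from exact cancellation. They also need a mediator that the intervention improves but that raises weight. Nothing in the protocol predicts this: section 2.2.5.1 presents self-efficacy and social support as reinforcing each other, and with paths in the same direction the screen costs about four percentage points. This stands and limits the expected harm. It does not rescue the rule, because the plan itself sets out to test suppression.

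The collinearity worry is not empty. Counting diet and exercise separately, Table 2 yields about five questionnaire scores and three adherence counts. Entering all of them together would be unsound, because the adherence counts arise only from intervention contact and largely duplicate study arm. As an illustration, assume mean attendance of 11-16 of the 22 sessions, SD 7-5, and zero in controls. Arm then explains (mean²/4)/(mean²/4 + SD²/2) = 55-84% of the variance in attendance. The variance inflation factor on the direct effect is 2.2-6.1, and its standard error is 1.5-2.5 times larger.

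Finally, these analyses are exploratory, and an entry threshold may properly be left to a statistical analysis plan. The entry rule is different: the protocol fixes it.

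**Conclusion.** The point holds in limited form. The entry rule tends to miss mediators with little effect alone, which conflicts with the stated purpose of the model, and it can bias the retained indirect effect and percentage mediated. The loss ranges from nearly complete at exact cancellation, through roughly half in intermediate cases, to a few points where each mediator shows alone at low correlation or both act in the same direction. The path values, correlations, arm effects and 10% threshold are all assumptions; only the algebra does not depend on them.

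Severity is low. The exploratory label limits the consequences but does not justify the screen: when the aim is to generate hypotheses, a missed pathway is the costlier error, and the candidate variables are already pre-specified. The primary analysis, its error rate and the sample size are unaffected.

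**What to change.** In section 2.2.9.1, replace the entry rule. Fit the multiple-mediator model with all pre-specified questionnaire mediators (the self-efficacy and social-support measures in Table 2) whatever their single-mediator result. Report the single-mediator models alongside, and give variance inflation factors as the check on collinearity.

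Handle the adherence measures separately, for example as associations with weight change within the intervention arm, and describe them as such rather than as mediated effects.

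Where an indirect effect and the direct effect have opposite signs, report both in kg with confidence limits instead of a percentage mediated.

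The cost is a few sentences and no new data. Intervals in the joint model will be somewhat wider if the questionnaire scores are strongly correlated.

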#### 2.2.9.2. Sample size and data interpretation

We power this trial on change in weight in kg from baseline to 24 months (primary endpoint). To estimate power, we use a *t*-test with simplified assumptions that compares (24m - baseline) differences between study arms at  $\alpha = 5\%$  (2-sided). Actual power may be greater due to increased efficiency associated with repeated-measures mixed models with baseline and covariate adjustments. A sample of 93/arm has 80% power to detect a net between-treatment *M* (SD) difference of 2.1(4.6) kg, assuming up to a 20% loss to 24 months of follow-up. As a conservative estimate, this effect size is based on the net weight change in the E-LITE self-directed intervention (corresponding to a mean of 4.5kg, 5.0% weight loss vs. 2.4kg, 2.6% in usual care), which was significantly smaller than that of the coach-led group (6.3 kg-; 6.6% weight loss). Weight loss  $\geq 5\%$  is widely regarded to be clinically significant, whereas a weight change  $< 3\%$  has been used to define weight maintenance. Hence, the net weight change for the E-LITE self-directed intervention relates to the minimal clinically important difference in weight reduction. To preserve statistical power, no multiplicity adjustment will be made for secondary analyses. These analyses are not intended to produce clinically actionable results, but to supplement conclusions based on the primary analysis, and to inform future research. They will be interpreted properly within that context, considering the totality of evidence available.

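### The percentage mediated is calculated only for significant mediators, which inflates the published percentages when power for a mediator is low to moderate

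*Protocol*

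**What the plan says.** The mediation plan is in Protocol section 2.2.9.1. Each candidate is first tested alone by the product of coefficients, and "Asymmetric confidence limits will be constructed based on the distribution of the product with the PRODCLIN program". Neither step depends on a significance result. Two later steps do:

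- Entry to the joint model: "Multiple-mediator models including all variables that are at least marginally significant in the single-mediator models" are used to look for independent and suppression effects.
- Extent of mediation: the mediated share of the total effect "will be calculated for each significant mediator" as αβ/(αβ + γ), where γ is the direct effect of the intervention.

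The section closes by calling these analyses "hypothesis generating only, but we pre-specify the variables to ensure a focus". Section 2.2.8.2 and Table 2 name the candidates: self-efficacy (more than one instrument), social support and intervention adherence. The section gives no caution about selection and plans no percentage for mediators that miss significance.

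**The concern.** An estimate that is shown only when it passes a significance test is biased away from zero, and most so when power is low. The trial was sized for the total effect on weight, and no power is stated for any mediator. Several candidates are each examined both longitudinally and contemporaneously. Section 2.2.9.2 adds: "To preserve statistical power, no multiplicity adjustment will be made for secondary analyses". There are therefore many opportunities for an estimate that is large by chance to pass.

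The percentage is the figure that the protocol itself chooses to express the extent of mediation. If the published percentages are a selected set, they overstate how much of the effect runs through weak or moderate mediators. A mediator without a percentage may be taken as unimportant when its estimate is merely imprecise.

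**Working it through.** **Inputs from the protocol.** Section 2.2.9.2 gives 93 per arm, a difference of 2.1 kg, SD 4.6 kg, two-sided 5% and up to 20% loss. Section 2.2.9.1 gives the product test and the share formula.

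**Reproducing the stated power.** Completers: 93 × 0.80 = 74.4 per arm, about 149 in all. The standard error is 4.6 × √(2/74.4) = 0.754 kg, and 2.1/0.754 = 2.78. Power is 79.5% by the normal approximation and 79.0% by the t-test. The stated 80% is reproduced to within rounding.

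**Assumptions.** The protocol gives neither the effect of arm on a mediator (a) nor that of a mediator on weight (b), so both are assumed, in SD units. It states no level for a significant mediator; two-sided 5% is assumed. The total effect is 2.1/4.6 = 0.457 SD. The true indirect effect is a × b, the true share is a × b/0.457, and the direct effect is the remainder. The fitted single-mediator model is correctly specified, the share uses the protocol's formula, and significance comes from 95% Monte Carlo limits for the product, standing in for PRODCLIN. Any inflation is then due to selection alone.

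**Four settings, 3,000 simulated trials each, 149 completers**

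| a, b | Power | True a×b | Mean a×b if significant | Ratio | True share | Median share if significant |
|---|---|---|---|---|---|---|
| 0.3, 0.2 | 28% | 0.060 | 0.113 | 1.9 | 13.1% | 22.3% |
| 0.3, 0.3 | 42% | 0.090 | 0.138 | 1.5 | 19.7% | 27.0% |
| 0.4, 0.2 | 44% | 0.080 | 0.122 | 1.5 | 17.5% | 24.9% |
| 0.5, 0.25 | 71% | 0.125 | 0.149 | 1.2 | 27.4% | 30.9% |

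**A wider grid: 16 settings, 6,000 trials each, 74 per arm, a = 0.3, 0.4, 0.5 or 0.8.** Ranges run over the four values of a. The last column also requires a significant total effect.

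| True share | Power for mediator | Median, all trials | Median, mediator significant | Median, mediator and total significant |
|---|---|---|---|---|
| 10% | 10–18% | 9–10% | 21–34% | 20–31% |
| 20% | 26–54% | 19% | 26–37% | 24–33% |
| 30% | 43–77% | 29–30% | 33–39% | 30–38% |
| 50% | 47–94% | 49–50% | 51–59% | 46–58% |

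Without the filter the median share is close to the truth throughout. With it, the median is higher in all 16 settings. The gap is 24 points (33.9% against 9.8%) at 10% power, 2.1 points (51.4% against 49.3%) at 87% power, and 1.5 points (50.8% against 49.3%) at 94% power.

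**Direction when the total effect must also be significant.** At a true share of 50%, a = 0.5 gives 47.6% and a = 0.8 gives 46.1%, both below the truth. The same trials without the mediator filter give 46.0% and 45.0%. The downward shift therefore comes from the condition on the total effect. The mediator filter still pushes the share up, by 1.6 and 1.1 points.

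**The case against.** The strongest reply has four parts.

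1. *Only a ratio is withheld.* A reader might infer that non-significant mediators are left with no stated size. The protocol does not support that: every candidate is tested alone, and the limits for the product carry no significance condition. This part stands, and the point is confined to the percentage.

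2. *The shares are not always inflated.* A reader might infer that every published share is too high. That is not so either. The filter does almost nothing for a strong mediator, and where the total effect must also be significant, a strong mediator's share can come out too low. The size depends on paths that the documents do not give. Intervention adherence in particular is an intervention process measure, which a modest SD difference between arms does not describe well. This part stands as a limit on size. It does not remove the inflation at low to moderate power.

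3. *Withholding an unstable ratio is defensible.* In simulation, 3–9% of the shares from non-significant mediators fell outside 0–100%. PRODCLIN gives limits for the product and not for the ratio, so showing every percentage takes more than a change of wording. This stands and shapes the remedy. Instability is better handled with an interval and a flag than with a filter that biases what remains.

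4. *The analysis is exploratory.* The protocol says so, and says that secondary analyses are meant to supplement the primary conclusion and not to direct practice. This limits the consequence but does not unbias an estimate. Exploratory work is most useful when all pre-specified estimates are shown.

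**Conclusion.** The point holds for the percentage mediated only. The protocol itself fixes significance as the condition for calculating it, so this is a stated rule and not a detail left to a later document. With about 149 completers and assumed paths, the rule inflates the reported share when power for the mediator is low to moderate: for example, from a true 13% to a median of about 22%, or from 17.5% to about 25%. At about 90% power or more the gap is 1 to 2 points. The direction for strong mediators can reverse if the total effect must also be significant. The figures rest on assumed path sizes, a correctly specified single-mediator model and a 5% level for the product test. The extra selection from the entry rule for the joint model was not simulated. This is a minor, inexpensive improvement to an exploratory analysis, and nothing here touches the primary comparison of weight at 24 months.

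**What to change.** Delete the significance condition in section 2.2.9.1. State instead that, for every pre-specified mediator and whatever its P value, the report will give:

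- the indirect effect αβ with its PRODCLIN limits, as the main measure of extent;
- the percentage of the total effect mediated, with a bootstrap or Monte Carlo interval, flagged as unstable where the interval is very wide or the value lies outside 0–100%.

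Cost: the single-mediator models are already planned for every candidate, so no new data or models are needed. The interval for the ratio is a small extra analysis. The downside is that wide or out-of-range percentages for weak mediators will be visible and need a sentence of explanation.

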#### 2.2.9.2. Sample size and data interpretation

We power this trial on change in weight in kg from baseline to 24 months (primary endpoint). To estimate power, we use a *t*-test with simplified assumptions that compares (24m - baseline) differences between study arms at  $\alpha = 5\%$  (2-sided). Actual power may be greater due to increased efficiency associated with repeated-measures mixed models with baseline and covariate adjustments. A sample of 93/arm has 80% power to detect a net between-treatment *M* (SD) difference of 2.1(4.6) kg, assuming up to a 20% loss to 24 months of follow-up. As a conservative estimate, this effect size is based on the net weight change in the E-LITE self-directed intervention (corresponding to a mean of 4.5kg, 5.0% weight loss vs. 2.4kg, 2.6% in usual care), which was significantly smaller than that of the coach-led group (6.3 kg-; 6.6% weight loss). Weight loss  $\geq 5\%$  is widely regarded to be clinically significant, whereas a weight change  $< 3\%$  has been used to define weight maintenance. Hence, the net weight change for the E-LITE self-directed intervention relates to the minimal clinically important difference in weight reduction. To preserve statistical power, no multiplicity adjustment will be made for secondary analyses. These analyses are not intended to produce clinically actionable results, but to supplement conclusions based on the primary analysis, and to inform future research. They will be interpreted properly within that context, considering the totality of evidence available.

#### 2.2.10. Data Management and Quality Control

All study data will be entered into computerized data files utilizing: (1) Microsoft ACCESS for data entry on recruitment, follow-up, and intervention tracking; (2) REDCap hosted at the PAMF Research Institute for self- and interviewer-administered questionnaire data and physical measurements; (3) the Nutrition Data System for Research (NDS-R) (Minneapolis, MN) licensed for data collection and nutrient analysis based on multiple-pass 24-hour diet recalls; and (4) a custom-designed web application for seven-day physical activity recall. All of the data entry systems will employ automatic, real-time range, logic, and missing value checks. Also, the outcome assessors are trained on data collection protocols (e.g., multiple-pass 24-hour diet recall using NDS-R and 7-day physical activity recall), and their performance is continuously monitored. Data sets will be cleaned, verified and archived, and then read into SAS (version 9.2, SAS Institute, Cary, NC) data sets, which also will be archived. One official copy of all the study data and a master data dictionary will be maintained and updated regularly by the study data analyst. All analytic and tracking databases will be stored in a password-protected, encrypted network drive with continuous backups. For the protection of participant confidentiality, unique anonymous study IDs will be used for data storing, tracking and reporting. Protected health information will be stored separately from all other study data, and will be used and disclosed in accordance with the Health Insurance Portability and Accountability Act regulations. Regular reports will be produced on (1) patient accrual and follow-up completion/retention in relation to goals and timeline; (2) the randomization process and group comparability on the balancing variables; (3) key baseline characteristics of the sample, by (blinded) group, related to the primary and secondary outcome variables and proposed effect modifiers and mediators; (4) intervention exposure and adherence; and (5) protocol violations. Any observed delays in these processes or data irregularities will be followed up and resolved in a timely manner.

